### Sample size

Due to the lack of data in the tICrH population alone, event rate data was calculated from a post-analysis of a trial assessing patients with a major bleed while on a DOAC (64% of whom had an intracranial haemorrhage).^20^ The reported re-bleeding rate was around 4%, thrombotic event rate 9.7%, and composite event rate (including death) of 13.6% at 30 days. Just under 1/3 of patients had re-started their anti-thrombotic by 30 days and no thrombotic events occurred after re-starting DOACs. When using a landmark analysis to compare patients who re-started their DOAC versus not restarted, a 14-day cut-off had a HR of 0.384 for composite events. This suggests a 60% reduction in events if restarting by 2 weeks, and likely to be greater for restarting at 1 week. The haemorrhagic events they were similar between those who had restarted (4%) and not (4.4%).

We have extrapolated these data to our cohort with a combined event rate of 12% (3% haemorrhagic and 9% thrombotic events within 12 weeks of tIcH) in the 4-week restart group and a 6% absolute reduction in the 1-week restart group (3% and 3%), assuming a significant reduction of thrombotic events without an increase in haemorrhagic events. Using a group sequential design with a single interim analysis after 50% of patients have reached 12 week follow-up or experienced an event. Sample size calculations were undertaken in SAS software version 9.4 with SAS/STAT package 14.3. The O’Brien-Fleming spending function, based on standardised Z-statistics, was used to determine the efficacy and futility boundaries (non-binding). For an overall two-sided 5% significance level and 90% power, 487 participants are required per group. To allow for 10% loss to follow-up, the total was increased to 542 per group (1084 in total).

### Randomisation

Randomisation lists were produced by an independent statistician at the Liverpool Clinical Trials Centre (LCTC), who is otherwise not involved in the trial. The trial uses restricted randomisation with variable block lengths, a 1:1 allocation ratio, and stratification by site, injury severity and frailty. Participants will be randomised via a secure web-based randomisation system centrally controlled by the LCTC once eligibility criteria have been confirmed, informed consent has been obtained, and pre-randomisation baseline assessments have been completed. The randomisation system will be established, maintained and monitored independently of the trial statistician and other trial staff. Personnel responsible for enrolling participants will not have access to the allocation sequence, and assignment to intervention groups will be performed by independent staff separate from those involved in enrolment, ensuring that allocation remains unbiased.

### Data collection and management

Trial outcomes will be assessed using validated instruments, including the Simplified Modified Rankin Scale, Barthel Index, Extended Glasgow Outcome Scale, Rockwood Frailty Score and EQ-5D-5L (Health Related Quality of Life score) (online supplementary table 1).^21–25^ Clinicians will be involved in the radiological and clinical evaluation of haemorrhagic and thrombotic events. Baseline data collection will include demographic characteristics, medical history, vascular risk factors, functional assessments and neuroimaging scored using the Liverpool Head Injury Tomography Score.^26^ Outcomes will be collected at predefined time points (baseline, 6, 12 and 26 weeks) using standardised electronic case report forms and questionnaires (figure 1).^27^ All data will be entered by authorised site staff into a secure, web-based trial database, with programmed validation checks and central monitoring to ensure accuracy and completeness. To enhance participant retention and ensure complete follow-up, participants will be contacted after randomisation by text, email or telephone to encourage adherence to the assigned intervention and scheduled assessments. In cases of missed visits, sites will attempt to contact the participant and reschedule the missed visit within 2 weeks. Before a participant is deemed to be lost to follow-up, site research staff will make every effort to regain contact with the participant and document in patient clinical records. Any participants lost to follow-up will be recorded in the trial database.

**Figure 1 F1:**
[figure not shown]
Trial Flowchart.

### Statistical methods

All analyses will follow the principle of intention-to-treat, as far as practically possible, and this approach will be applied to both the primary and secondary outcomes. Missing data will be actively monitored throughout the trial. Strategies will be implemented to minimise missingness, and the reasons for missing data will be systematically recorded to inform the appropriate handling of missing data in the analysis.

A single interim analysis will be conducted once 50% of the total participants have been recruited and followed up to 12 weeks, or once an event has been observed, whichever occurs first (to allow primary outcome to be analysed). Non-binding stopping boundaries will be applied using the O’Brien–Fleming spending function based on standardised Z-statistics, with efficacy and futility boundaries set at 2.963 and 0.345, respectively.

The primary outcome: proportion of patients experiencing a haemorrhagic or thrombotic event following tICrH, will be analysed using logistic regression adjusted for the randomisation factors. A sensitivity analysis will be performed using the safety analysis set. Secondary time-to-event outcomes will be analysed using Cox proportional hazards models or competing risks analyses, as appropriate. Quality of life and functional outcomes will be analysed using longitudinal models, with joint modelling considered where appropriate. Statistical significance will be defined as p<0.05.

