### Trial design

This trial is designed as a multicentre, pragmatic, parallel-group, two-arm, superiority, randomised controlled trial (RCT), with 1:1 allocation ratio, stratified by recruitment site, injury severity (Glasgow Coma Score >12 or ≤12) and frailty assessed via the Rockwood Clinical Frailty Scale (0–4 or 5–9). The study is a Type A CTIMP (Clinical Trial of Investigational Medicinal Product): no higher than that of standard medical care. Participants will be identified and recruited across at least 20 trauma networks in the UK (https://restart-trial.org.uk). Eligible participants are adults with tICrH who were receiving oral anticoagulation as part of their routine medications prior to admission, regardless of when the last dose was taken. Full inclusion and exclusion criteria are summarised in table 2.

**Table 2 T2:** Eligibility criteria for participation in the trial

Category	Criteria
Inclusion criteria	Informed consent obtained from participant or participant’s legal representative and ability to comply with the requirements of the trial. Adults ≥18 years with traumatic intracranial haemorrhage (tICrH) within the past 1 week who were taking an OAC prior to admission. Oral anticoagulants include any direct oral DOAC or VKA (eg, warfarin), prescribed for AF or VTE prior to admission for tICrH.
Exclusion criteria	Traumatic intracranial haemorrhage limited to chronic subdural haematoma only. Patients with a mechanical heart valve. Plan to start/restart antiplatelet therapy within 12 weeks of tICrH. Abbreviated Injury Scale other than head with a score >3. Pregnant or breast-feeding female. Participants of reproductive potential (male or female) unwilling to use a reliable means of contraception. Hypersensitivity or contraindication to DOAC as detailed in the Investigational Medicinal Product Summary of Product Characteristics (SmPC). Ongoing bleeding where it would be unsafe to restart DOAC at 1 week. Clinical reason requiring DOAC restart before 4 weeks or beyond the 12-week study period. Indication to remain on VKA rather than switching to DOAC (eg, severe renal impairment or mechanical heart valve).

AF, atrial fibrillation; DOAC, direct oral anticoagulant; OAC, oral anticoagulant; VKA, vitamin K antagonist; VTE, Venous Thromboembolism.

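### The blanket p<0.05 rule ignores the alpha spent at the interim look, so the final primary test as written exceeds the stated overall two-sided 5%

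*Protocol article*

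**What the plan says.** The Sample size section sets up the design: "Using a group sequential design with a single interim analysis after 50% of patients have reached 12 week follow-up or experienced an event". It names the O'Brien-Fleming spending function for efficacy and futility, calls the boundaries non-binding, and states the target: "For an overall two-sided 5% significance level and 90% power, 487 participants are required per group".

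The Statistical methods section repeats the spending function and gives interim values only: "efficacy and futility boundaries set at 2.963 and 0.345". The next paragraph opens with the logistic regression for the primary outcome, goes on to the sensitivity, time-to-event, quality-of-life and functional analyses, and closes with "Statistical significance will be defined as p<0.05". That sentence does not exempt the primary outcome and does not call 0.05 an overall level. The article gives no final critical value and no adjusted final p threshold.

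**The concern.** In a group sequential design, the interim and final looks share the overall 5%. Whatever the interim efficacy boundary spends is no longer available at the end, so the final nominal threshold must lie below 0.05. As written, the final primary test uses the full 0.05 in addition to what the interim has already spent.

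At stake is the rule that decides the trial. A final primary p just under 0.05 would be significant under the Statistical methods sentence but not under the design in the Sample size section. An ordinary 95% confidence interval would carry the same mismatch, because it could exclude no effect when the group sequential test does not reject. If the conflict is found only after unblinding, either choice of threshold will look post hoc.

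**Working it through.** **Inputs**

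- Overall two-sided alpha 0.05, power 90%, 487 per group (Sample size).
- One interim look, taken at information fraction t = 0.5 (Sample size).
- Interim boundaries 2.963 (efficacy) and 0.345 (futility), non-binding (Statistical methods; Sample size).
- Event rates: "combined event rate of 12% (3% haemorrhagic and 9% thrombotic events within 12 weeks of tIcH) in the 4-week restart group", and 6% in the 1-week group (Sample size).
- Stated significance rule p<0.05, that is |Z| > 1.960 (Statistical methods).

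**Step 1: reproduce the interim boundary.** The O'Brien-Fleming-type spending function with 0.025 per side is

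α(t) = 2[1 − Φ(z₀.₉₈₇₅/√t)].

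At t = 0.5: 2.2414/0.7071 = 3.170, so α = 0.001525 per side, or 0.00305 two-sided. The boundary is Φ⁻¹(1 − 0.001525) = 2.9626, which matches the stated 2.963. The classical O'Brien-Fleming boundaries (2.797 interim, 1.977 final) do not match, so the design is the spending-function version.

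**Step 2: find the final boundary that this design implies.** Under the null hypothesis, Z₁ (interim) and Z₂ (final) are bivariate normal with correlation √0.5. Futility is non-binding and earns no credit. The final value c solves

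P(|Z₁| > 2.963) + P(|Z₁| ≤ 2.963, |Z₂| > c) = 0.05.

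The first term is 0.00305, which leaves 0.04695 for the second. Numerical integration gives c = 1.9686, a nominal two-sided p of 0.0490.

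**Step 3: overall error under the rule as written.** With c = 1.960 the same sum is 0.00305 + 0.04794 = 0.05099, or 5.10%. A simulation of 20 million trials gave 0.0509.

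**Step 4: check against the sample size.** With unpooled variance, the standard error at 487 per group is √[(0.12×0.88 + 0.06×0.94)/487] = √(0.162/487) = 0.01824, so the expected Z is 0.06/0.01824 = 3.290. Power, with the trial stopped for futility when |Z₁| < 0.345:

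| n per group | final 1.969 | final 1.960 |
|---|---|---|
| 484 | 89.84% | 89.97% |
| 485 | 89.90% | 90.03% |
| 486 | 89.95% | 90.09% |
| 487 | 90.01% | 90.14% |

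The stated 487 is the smallest size that reaches 90% with 1.969; with 1.960, 485 would have been enough. The sample size therefore points to 1.969 as the final value used in the calculation.

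**Step 5: sensitivity to interim timing.** If the interim boundary is recomputed from the spending function at the actual information fraction:

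| t at interim | final critical value | nominal p | overall error if p<0.05 is used |
|---|---|---|---|
| 0.5 | 1.969 | 0.0490 | 5.10% |
| 0.6 | 1.981 | 0.0476 | 5.23% |
| 0.7 | 2.000 | 0.0455 | 5.41% |

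**The case against.** **The sentence may mean the overall level.** It closes a paragraph that covers every analysis, and the spending function already fixes the final boundary once alpha and timing are known. That may well be the intention. But the overall level is stated elsewhere, in the Sample size section, and this sentence defines significance for p-values straight after the analysis models. A reader would apply it to the final primary test.

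**The final boundary belongs in the analysis plan.** Leaving it out would be acceptable in a condensed article. The difficulty is that the article does state a threshold, and that threshold conflicts with its own design. An analysis plan giving 0.0490 would then contradict the published protocol.

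**Futility stopping compensates.** If the 0.345 boundary were always obeyed, a final test at 1.960 would give 4.92%. The arithmetic is right, but the protocol calls the boundaries non-binding, so that reduction cannot be counted. The 5.10% applies when futility is not enforced, which is the case that alpha control has to cover.

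**The 487 does not prove 1.969.** The document does not print a final value, so this remains an inference. It also depends on convention: if a result below −0.345 at the interim is treated as stopped as well, power at 487 is 89.96%. The finding does not depend on this point.

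**The effect is negligible.** It is small, and this stands. It limits the weight of the point but does not remove the contradiction.

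**Conclusion.** The point holds. The stated significance rule for the final primary analysis is inconsistent with the stated overall two-sided 5% and with the trial's own interim boundary. Overall type I error is 5.10% instead of 5.00%, and the two rules disagree only for a final p between 0.0490 and 0.0500. The interim boundary itself reproduces and needs no change; the fault lies in the unqualified p<0.05 sentence.

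The result assumes O'Brien-Fleming-type spending with 0.025 per side (confirmed by the match to 2.963), an interim at 50% information, asymptotically normal test statistics, and no credit for non-binding futility.

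**What to change.** Replace the blanket rule in Statistical methods with wording such as: *For the primary outcome, significance at the final analysis requires |Z| ≥ 1.969 (two-sided p<0.0490), or the value recomputed from the O'Brien-Fleming spending function at the actual interim information fraction, with a confidence interval at the matching level. For secondary outcomes, p<0.05 is used.* With the interim at 50%, the matching interval is 95.1% (1 − 0.0490).

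The cost is one sentence in the protocol, carried into the analysis plan. Sample size, interim boundaries and data collection are unaffected. The article reports that recruitment is ongoing, so the change can be recorded before the results are known.

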### Economic methods

The economic evaluation will adopt the perspective of the National Health Services and Personal Social Services operating in the UK. A resource use questionnaire that includes items relating to primary, hospital care and personal social care services will be administered during clinic visits or calls at baseline, 6 weeks, 12 weeks and 26 weeks (online supplemental file 2). If a participant’s condition prevents self-completion, caregivers will assist in completing them on the participant’s behalf where possible, ensuring the participant’s input is captured. For trial participants receiving care in England, use of hospital care services will be obtained via requests for bespoke Hospital Episode Statistics to NHS Digital England at the end of the trial. Unit costs will be obtained from the NHS reference costs,^28^ the compendium of Unit Costs of Health and Social Care and the British National Formulary.^29^ Costs will be based on the most recent available at the time of analysis.

Health outcomes will be assessed from participants’ responses to the EQ-5D-5L questionnaire, administered at baseline, 6 weeks, 12 weeks and 26 weeks. Utilities will be calculated using the National Institute for Health and Care Research preferred method at the time of analysis (currently the 5 L/3 L cross-walk tariff.^30^

Patient-level cost and utilities will be analysed using regression models, taking into account a lack of baseline utility score, to estimate mean values associated with clinically meaningful health states.^31^ These states will be the basis of a Markov model to extrapolate costs and consequences over patients’ lifetime.^32^ While the base-case economic evaluation will adopt a lifetime horizon of analysis, we will also report costs and quality-adjusted life year, and estimate the incremental cost-effectiveness ratio over the 26-week follow-up period of the trial.

A stochastic sensitivity analysis will be carried out to assess the probability of cost-effectiveness for given threshold values of willingness to pay. This will consider simultaneous uncertainty in parameter inputs and provide evidence suitable to decision makers on the cost-effectiveness of restarting DOACs at different times. Additional sensitivity and scenario analyses will be undertaken to account insofar as possible, different sources of uncertainty.

### Oversight and monitoring

The Liverpool Clinical Trials Centre (LCTC) acts as the Clinical Trials Unit and is responsible for day-to-day trial management, including data management, operation of the randomisation system, central monitoring and safety reporting on behalf of the Sponsor.^33^ LCTC is part of the University of Liverpool (https://lctc.org.uk). Trial management, monitoring and analysis functions are delivered centrally, including expedited regulatory safety reporting and operational support to participating sites. Strategic oversight is provided by an independent Trial Steering Committee (TSC), which reviews trial conduct, considers recommendations from the IDSMC, and advises the sponsor and funder on the continuation or modification of the trial. The IDSMC provides recommendations regarding trial continuation or modification, such as confirming study assumptions or proposing adjustments to the sample size.

## Ethics and dissemination

The study was approved on 14 October 2024 by the Berkshire Research Ethics Committee (reference: 24/SC/0298). Written informed consent will be obtained from all participants prior to enrolment (online supplemental file 3). Participant data will be collected and processed in accordance with the UK GDPR (General Data Protection Regulation) and the Data Protection Act 2018. Identifiable information will be stored securely and transferred separately from pseudonymised clinical data, which will be coded with a unique trial identifier. Access will be restricted to authorised members of the research team, and all data will be stored on secure servers. Substantial amendments to the protocol or participant-facing materials will be submitted to the Research Ethics Committee, Health Research Authority, Medicines and Healthcare products Regulatory Agency, and participating sites for approval prior to implementation. Approved changes will be circulated to investigators and documented through version control in the Trial Master File amendment history.

The results of the trial will be disseminated to participants, healthcare professionals, policy-makers and the wider public. Findings will be submitted for publication in peer-reviewed journals and presented at scientific conferences. Trial outcomes will also be reported in the trial registry in accordance with regulatory requirements. The trial is embedded in routine NHS practice and does not impose additional research imaging or procedures beyond standard clinical care; CT/MRI scans are limited to those performed for usual management. The end of trial is defined as database lock, after which standard site and trial closure procedures are undertaken. Participants will continue with their usual clinical care team after the trial closes.

## Discussion

The aim of this trial is to determine the optimal timing for restarting DOAC therapy following tICrH in adults who were anticoagulated prior to injury. The decision of when to restart anticoagulation represents a complex clinical dilemma that balances the competing risks of re-bleeding and thromboembolic complications. Studies suggest that early tICrH expansion (within 48 hours) on routine repeat imaging occurs in 10–37% of patients on OACs, supporting the need for temporary cessation of anticoagulation during the acute phase.^10
34^ This risk, however, reduces substantially over time.

Withholding anticoagulation for prolonged periods exposes patients to an increased risk of thrombotic complications such as stroke, myocardial infarction and venous thromboembolism.^35^ A trial of 352 patients suffering a major bleed while on a DOAC demonstrated that thrombotic events increased from approximately 4% at 1 week to 10% at 4 weeks.^36^ At 3 months, patients who had restarted anticoagulation experienced fewer strokes (HR 0.85, 95% CI 0.43 to 1.68) and deaths (HR 0.50, 95% CI 0.35 to 0.72), despite a modest increase in bleeding risk (HR 1.62, 95% CI 0.95 to 2.75) compared with those who had not restarted.^37^

The absence of high-quality randomised data in this field limits clinical confidence in current practice. Given that most affected patients are not admitted to a neurosurgical unit, but rather managed in a local out-lying hospital, clear communication of advice on restarting times can be missing altogether and lead to prolonged time off anti-coagulation and greater harm. This trial addresses the evidence gap through a multi-centre, randomised controlled design comparing 1-week versus 4-week DOAC resumption and will generate the highest level of evidence to inform future clinical practice.

### Trial status

The trial achieved trial greenlight on 25/02/2025 and the first site opened on 27/02/2025. The first patient was recruited on 10/03/2025. Recruitment is ongoing.
